**5.12 Treatment Period (14 days + 1 day)**

Prescriptions or medical orders are issued by research physicians based on randomly assigned drug numbers. Drug administrators dispense medications to research nurses based on these prescriptions or medical orders. Upon retrieval of the medication, the research nurse administers the prescribed dosages to the participants on a daily basis, with the regimen spanning a continuous period of 14 days. Within the 1-day window following the end of this administration period, the following tasks must be completed and recorded:

- Conduct vital signs checks.
- Researchers document changes in condition, AEs, concurrent illnesses, and concomitant medication use during the medication period.
- Participants to complete the MMSE, GCS, MoCA, LOTCA, GOS-E, and the ADL-BI for evaluation.

**5.13 Follow-Up Visits**

30 days Follow-Up (± 3 days after medication ends):

- Researchers conduct a telephone follow-up to assess the participant's ADL-BI. The evaluation is obtained by interviewing the participant or their guardian.

60 days Follow-Up (± 3 days after medication ends):

- Similar to the 1-month follow-up, researchers use a telephone interview to assess the participant's ADL-BI by speaking with the participant or their guardian.

90 days Follow-Up (within ± 3 days window after medication ends); Participants are required to visit the clinic, where the following procedures are carried out and documented:

- Vital signs are checked.
- CT or MRI scans are performed; these should be consistent with those done during the screening period.
- Collection of blood and urine samples to measure routine blood values (WBC, RBC, HGB, PLT), routine urine values (PRO, GLU, LEU, ERY), liver function (AST, ALT, TBIL, γ-GT, ALP), kidney function (Scr, GFR), coagulation function (PT, APTT, TT, FIB), CK, and TG. A 12-lead ECG is performed, and blood pregnancy tests are conducted for women of childbearing age.
- Participants complete cognitive and functional assessments including the MMSE, MoCA, LOTCA, GOS-E, and the ADL-BI.

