**5.6 Trial Period**

Screening period (-72h to 0h) + Treatment period (14+1 days) + Follow-up period of 90 Days.

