**7 Endpoints evaluation criteria**

**7.1 Efficacy** **Endpoints:**

7.1.1 Primary endpoint

- The primary outcome measure is the change in scores on the LOTCA at 90 days post-treatment compared to baseline.

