**8.3 Management and Documentation of** **Adverse Events**

8.3.1 Management of Adverse Events

- Inpatients

If an AE occurs during a subject's hospital stay, it should be handled according to the following procedure:

Upon detecting an AE in a subject, the attending or on-duty doctor should promptly inform the researcher. If necessary, symptomatic treatment may be initiated first. The research physician should preliminarily assess the severity and relation to the investigational drug and provide further handling advice:

- - General AE: Close monitoring of the event's outcome or corresponding symptomatic treatment may be conducted;
  - Significant AE: The research physician should immediately inform the principal investigator. Based on the subject's condition, treatment may be temporarily suspended, medication dosage adjusted, or targeted treatment measures taken. If necessary, the principal investigator may decide whether to urgently unblind (if applicable);
  - SAE: Handled and reported according to the following "8.7".
  - The research physician should treat according to the medical condition, and if the subject's injury exceeds the treatment capabilities of the research department, consultation and assistance from relevant departments should be sought.
- Outpatients

Upon learning of an AE in a subject, the research physician should thoroughly inquire about the subject's symptoms, signs, and location at the time of the event and provide necessary explanations and guidance. An initial assessment of the severity and relevance of the AE should be made. If the subject is at a local medical institution, the physician should contact the attending doctor by phone to re-assess the severity of the AE and provide handling advice:

- General AE: Initial treatment at a local hospital may be advised, with a notification to closely monitor the outcome of the event;
- Significant AE: It is suggested that the subject return to the hospital for treatment or seek treatment at a local hospital, and promptly inform the principal investigator. If the local hospital's facilities are limited, a doctor should be sent for treatment. If necessary, log in to the Interactive Web Response System (IWRS) to initiate the unblinding procedure. Treatment suspension, medication dosage adjustment, and symptomatic treatment should be adopted as per the protocol requirements.

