**10 Sample size calculation**

Before conducting this study, we conducted a pilot trial: The change values of the total scores on the LOTCA scale at 90 days post-drug cessation compared to baseline for L-oxiracetam and oxiracetam were 26.0 ± 11.8 and 22.8 ± 10.0, respectively. The combined standard deviation (SD) for both groups was 11.0, with α set at 0.05 and 1-β at 0.8. Employing an optimal design with a sample ratio of 1:1, PASS software calculated a sample size of 190 cases for each group.

The change values of the total scores on the LOTCA scale at 90 days post-drug cessation compared to baseline for the L-oxiracetam group and the placebo group were 26.0 ± 11.8 and 20.0 ± 11.4, respectively. The combined SD for both groups was 11.6, with α set at 0.05 and 1-β at 0.8. Employing an optimal design with a sample ratio of 2:1, PASS software calculated a sample size of 204 cases for the L-oxiracetam group and 102 cases for the placebo group.

Considering potential dropouts, we increased the sample size by 15%. Therefore, the sample sizes for the L-oxiracetam group, oxiracetam group, and placebo group were set at 236, 236, and 118, respectively.

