**14 Statistical analysis plan**

SAS 9.4 was used for data analysis independently conducted by a biostatistician unaware of the allocation. Continuous variables will be presented as mean ± SD with a 95% CI for normal distribution and as median (range) for abnormal distribution. Categorical variables will be expressed by numbers and percentages. All hypothesis tests were two-sided with α = 0.05. A P-value ≤ 0.05 indicated statistical significance.

The analysis for the primary outcome was conducted using analysis of covariance (ANCOVA). The least squares means of change from baseline at 3 months in LOTCA scores, as well as the mean differences between groups (L-oxiracetam vs. oxiracetam/ Placebo) and 95% CIs were estimated. Cohen’s d and 95% CI was used to calculate the effect size. For the secondary continuous efficacy outcomes, mean differences with corresponding 95% CIs were also analyzed using ANCOVA. For categorical outcomes of GOS-E, the rate differences and 95% CIs between groups were estimated using the approximate normality method and statistically tested with Fisher's exact probability test. All models were adjusted for age, sex, education, and TBI severity at baseline. Stratified analyses were performed to explore the efficacy of the L-oxiracetam intervention on cognitive function in patients with different age (< 60 vs. 60 + years), sex (male vs. female), education (none vs. Primary vs. Secondary school or Higher), and TBI severity (mild vs. moderate). Moreover, multiplicative interactions were tested by including a cross-product item in the model for the intervention group with age, sex, education, or TBI severity.

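### The primary LOTCA visit is counted from the end of medication, so a patient who stops drug early but stays in follow-up is assessed up to 13 days sooner after first dose than a completer

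*Protocol*

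**What the plan says.** Three places in the Protocol define the timing of the primary assessment, and all three count from the end of treatment:

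- Section 5.13: "90 days Follow-Up (within ± 3 days window after medication ends". The 30- and 60-day telephone ADL-BI assessments use the same anchor.
- Section 7.1.1: "The primary outcome measure is the change in scores on the LOTCA at 90 days post-treatment compared to baseline".
- Section 10, describing the phase II data behind the sample size: "at 90 days post-drug cessation compared to baseline".

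The planned course is fixed (section 5.12: "with the regimen spanning a continuous period of 14 days"), and section 5.6 sets out the blocks as "Screening period (-72h to 0h) + Treatment period (14+1 days) + Follow-up period of 90 Days". The course actually received can be shorter. Section 8.4 foresees discontinuation for moderate and severe adverse events, section 8.7.1 for serious ones where necessary, and section 8.7.3 on pregnancy.

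Section 13 keeps every randomised patient with at least one dose in the full analysis set. No section shown sets the Day 90 date from randomisation, first dose or injury, or says when an early stopper is due. The Trial Schedule has a footnote mark on its follow-up column whose text is not in the copy at hand, so nothing here rests on it.

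**The concern.** LOTCA change is measured in patients who are recovering from acute injury. The phase II placebo group gained 20.0 points (section 1.3.4.3), so elapsed time may account for a large part of the outcome. If the visit date moves with the last dose, a patient who stops early is tested at an earlier point of recovery than a completer.

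Stopping can depend on tolerability and clinical course, both of which treatment may affect. If one arm has more early stopping, that arm is on average assessed sooner and scores somewhat lower for that reason alone. Analysing patients as randomised does not correct this. Nor does the ANCOVA: its covariates are age, sex, education and TBI severity in section 14, and baseline, injury classification and education in the synopsis. None of these is time of assessment.

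The same 13-day shift affects the telephone ADL-BI calls, where it is a larger share of the interval: the 30-day call falls on Day 44 for a completer and Day 31 after a single dose.

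**Working it through.** **1. The plan's own figure.** The yardstick is the planning difference between L-oxiracetam and oxiracetam in section 10: 26.0 − 22.8 = 3.2 points, SD 11.0, two-sided α 0.05, power 0.80, allocation 1:1.

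n per group = 2 × (1.960 + 0.842)² × 11.0² / 3.2² ≈ 186

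The stated figure is 190, within about 2%, so 3.2 is the difference the trial was sized on.

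**2. Visit day.** Take first dose as Day 1. Then visit day = day of last dose + 90, with a window of ±3.

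| Last dose | Visit day | Window | Days before completer |
|---|---|---|---|
| Day 14 (completer) | 104 | 101–107 | 0 |
| Day 10 | 100 | 97–103 | 4 |
| Day 7 | 97 | 94–100 | 7 |
| Day 3 | 93 | 90–96 | 11 |
| Day 1 | 91 | 88–94 | 13 |

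For stops by Day 7 the whole window lies before the completers' window. From Day 8 (window 95–101) the two overlap, so the ±3 days absorb part of the shift.

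**3. Points lost per shifted patient.** The protocol gives no trajectory, so the shape of recovery is an assumption. All curves below reach the placebo gain of 20.0 at Day 104.

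- Linear: 20.0 / 104 = 0.192 points per day. A 13-day shift costs 0.192 × 13 = 2.5 points; a 7-day shift costs 1.35.
- Slowing recovery with half-life h: R(t) = 20 × (1 − e^(−kt)) / (1 − e^(−104k)), with k = ln 2 / h. A 13-day shift costs 20 − R(91), which is 0.10 points for h = 14 days, 0.70 for h = 30 and 1.39 for h = 60.

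**4. Bias in the arm comparison.** Bias = (difference between arms in the proportion stopping early) × (points lost per stopper). Assume an imbalance of 5 to 10 percentage points, with every excess stop after the first dose.

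| Recovery | 5 points' imbalance | 10 points' imbalance |
|---|---|---|
| Linear | 0.05 × 2.5 = 0.13 | 0.10 × 2.5 = 0.25 |
| Half-life 60 days | 0.07 | 0.14 |
| Half-life 30 days | 0.03 | 0.07 |
| Half-life 14 days | 0.005 | 0.01 |

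The linear row is 4% to 8% of the planning difference (0.125 / 3.2 and 0.25 / 3.2). Its upper end is 0.25 / 11.0 = 0.02 SD. If early stopping is balanced between arms, the bias is near zero whatever the curve.

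**5. After the change.** With one visit day counted from first dose, the scheduled difference between early stoppers and completers is 0 days. The sample size is unaffected.

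**The case against.** **The anchor may mean the scheduled end.** Section 5.6 lays out fixed blocks and section 5.12 describes a continuous 14-day course, so the end of medication could be taken as the end of the planned period. Every patient would then be due near Day 104. This reading is possible, but no section states it. The wording of section 5.13, and the reference to drug cessation in section 10, point at least as naturally to the patient's own last dose. That the text allows both readings is itself a reason to fix it.

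**Many early stoppers will have no Day 90 visit.** Section 4.3 makes serious or significant adverse events and poor compliance possible grounds for withdrawal. Section 4.3.3 then asks only for a last assessment where possible, and section 13 carries the last value forward. This stands: the anchor matters only for patients who stop drug and remain in follow-up. Carry-forward for the others is a separate issue, which re-anchoring the visit does not solve.

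**Ninety days off drug is a coherent endpoint.** It measures persistence and matches the phase II data used for planning. This also stands, and the proposed dates preserve it exactly for completers.

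**The size rests on stacked assumptions.** Linear recovery, all stops after dose one, and an arm imbalance that the protocol does not report are each unfavourable choices. This is why the figures are given as an upper range.

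A reader might infer two stronger points that the Protocol does not support:

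- *Section 14 contradicts section 5.13.* Section 14 has "The least squares means of change from baseline at 3 months in LOTCA scores", which could be taken as a visit about 14 days before the one in section 5.13. The Protocol uses months as shorthand for its post-treatment visits, however. Section 5.13 calls the 30-day call the 1-month follow-up. Section 1.3.4.3 reports the phase II means at three months after treatment, and section 10 gives the same means at 90 days after cessation. In section 14 the reference to baseline qualifies the change and does not start a clock.
- *Suspended patients are assessed late.* Section 8.3.1 says "treatment may be temporarily suspended, medication dosage adjusted, or targeted treatment measures taken", but nothing says whether missed doses are made up, and so whether the end date moves.

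**Conclusion.** The concern holds in a limited form. As written, the clock for the primary endpoint starts at a post-randomisation event, and a patient who stops early but is still followed is due up to 13 days before a completer. This biases the treatment comparison only if early stopping differs by arm. Under linear recovery and a 5 to 10 percentage-point imbalance concentrated on the first dose, the bias is at most about 0.13 to 0.25 LOTCA points. With slowing recovery (half-life 14 to 60 days) it is about 0.005 to 0.14. The recovery curves and stopping rates are assumptions, as the Protocol supplies neither. This is a minor improvement and does not threaten the trial's conclusions, but it removes a treatment-dependent clock from the primary endpoint at no real cost.

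**What to change.** In sections 5.13 and 7.1 and in the Trial Schedule, count follow-up from first dose, or equivalently from the scheduled end of the 14-day period, for every patient whatever the actual duration of treatment. With first dose as Day 1, the telephone ADL-BI calls fall on Day 44 and Day 74 and the clinic visit with the primary LOTCA on Day 104, each ±3 days. Add one sentence saying that patients who stop study drug but have not withdrawn consent are assessed on those same days.

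Section 10 describes phase II data and can stay as it is. The cost is wording only. Completers' dates do not change, no visit is added, the sample size is unaffected and no treatment rule is touched. The gain is confined to patients who stop drug and are kept in follow-up.

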**5.14 Unscheduled Visits**

During the trial, if a participant experiences any discomfort or adverse effects, an unscheduled visit should be arranged. This visit will allow for immediate assessment and management of any issues that arise, ensuring the participant's safety and well-being throughout the trial process.

These follow-up and unscheduled visits are crucial for monitoring the long-term effects and efficacy of the treatment, as well as ensuring the ongoing health and safety of participants.

**6 Concomitant Medications and Treatments**

**6.1 Basic Treatment**

Post-injury, standard treatments to control intracranial pressure and prevent complications from cranial injuries are permitted. However, it is mandatory to record in the eCRF details such as the generic names of medications or other therapies used, dosage, reasons for use, frequency, and timing. This data will be analyzed and included in the final report.

**6.2 Prohibited Medications and Treatments**

Post-injury cognitive rehabilitation treatments are not allowed. During the medication and follow-up periods, the use of drugs that might affect the efficacy evaluation is prohibited, including:

- Cholinesterase inhibitors such as donepezil, rivastigmine, galantamine, tacrine, and huperzine A.
- γ-lactam brain function enhancers, such as aniracetam, piracetam, oxiracetam, and other commercially available forms.
- Other medications such as nimodipine, vinpocetine, ginkgo biloba extracts, cerebrolysin, amantadine/ robenidine, gangliosides, citicoline, idebenone, amantadine, glutamic acid, erythropoietin injection, dihydroergotoxine, brain protein hydrolysates, murine nerve growth factor, pyritinol, acetylglutamine, piracetam, ethionamide, and hormone replacement therapy (growth hormones, estrogens, thyroid hormones).

**6.3 Permitted Medications and Treatments**

Symptomatic treatment of other comorbid diseases is allowed, provided it does not affect the evaluation of efficacy and safety. Such treatments must be documented in the eCRF, including generic names or names of therapies, dosage, reasons for use, frequency, and timing, to facilitate analysis and reporting.

Any medications used to treat AEs or for prophylactic purposes during the trial must be meticulously recorded in the eCRF.

**7 Endpoints evaluation criteria**

**7.1 Efficacy** **Endpoints:**

7.1.1 Primary endpoint

- The primary outcome measure is the change in scores on the LOTCA at 90 days post-treatment compared to baseline.

7.1.2 Secondary endpoints

The secondary outcome measures include:

- Changes in scores on the LOTCA and GCS at the end of treatment compared to baseline;
- Changes in scores on the MMSE and MoCA at the end of treatment and 90 days post-treatment compared to baseline;
- The percentage of subjects at each level of the GOS-E at the end of treatment and 90 days post-treatment;
- ADL-BI at the end of treatment, 30 days, 60 days, and 90 days.

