**2 Trial Objectives**

- Primary objectives
- To evaluate the efficacy of L-oxiracetam on functional outcome in patients with TBI.
- To evaluate the safety of L-oxiracetam in patients with TBI.
- Secondary objectives
- To analyse changes in function and disease severity of patients with TBI treated with either L-oxiracetam, oxiracetam or placebo.
- Exploratory objectives
- To evaluate influence in subgroup (such as age, gender and so on) in patients with TBI treated with either L-oxiracetam, oxiracetam or placebo.

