**4 Target Population**

**4.1 Eligibility of Target Population**

Patients are aged 18 to 75 years and have mild to moderate (GCS score of 10 to 15) acute TBI.

And investigators and sponsor should discuss with sharing sufficient information regarding the eligibility of patients before the enrollment.

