**4.2 Inclusion and exclusion criteria**

4.2.1 Inclusion criteria

- Age 18-75 years;
- Head injury meeting all of the following conditions: 1) Clear evidence of head trauma in the current diagnosis, including closed head injury or head injury with cerebrospinal fluid leakage and/ or ear or nasal leakage and/ or intracranial air accumulation; 2) Confirmed by magnetic resonance imaging (MRI) or computed tomography (CT) to have intracranial bleeding above the cerebellar tentorium (including cerebral contusion, subarachnoid hemorrhage, extradural hematoma, subdural hematoma, intracerebral hematoma, etc.), with or without transient loss of consciousness; 3) Classified as mild to moderate head injury (GCS: 10-15); 4) Stable condition within 72 hours after head injury, undergoing conservative treatment, not undergoing craniotomy (may have intracranial pressure monitoring without general anesthesia or basal anesthesia);
- MMSE score below normal, with diagnostic cutoff values depending on different educational levels: illiterate (no education) ≤ 19 points, elementary school level ≤ 22 points, junior high school and above level ≤ 26 points;
- Consent from the guardian and/ or patient to participate in this clinical trial and signing of the informed consent form.

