**5.8 Trial Procedure Related Assessments**

- Demographic data: Includes age, gender, and ethnicity.
- Medical history: Inquiry or collection from existing medical records about the current condition of cranial injuries and any other diseases the participant might have, including medication and allergy history.
- Medication history: Inquire about prescription and over-the-counter drugs used prior to the administration of the trial drug, recording the generic name of the drugs, single dose administered, frequency, method of administration, and reasons for use.
- Disease diagnosis: Cranial injuries confirmed by CT or MRI scans (participants who have already been examined post-injury do not need to repeat the scans).
- Vital signs: Include body temperature, respiration, pulse, and blood pressure.
- Biological sample collection and laboratory assessment: Collection of blood and urine samples for routine blood tests, blood biochemistry, coagulation functions, liver and kidney function tests, TG, creatine kinase (CK) measurements, blood pregnancy tests, and routine urinalysis. Biological samples are to be collected, processed, and tested by the laboratories of the participating units. Before the receipt of trial drugs, clinical trial units must provide the sponsor with the normal reference ranges for each laboratory indicator and promptly inform the sponsor of any changes during the trial.
- 12-lead ECG: Heart rate and QT/ QTc interval results must be reported.
- Scale assessment: Use of the GCS to evaluate the severity of cranial injuries in participants, the MMSE, Montreal Cognitive Assessment (MoCA), and LOTCA to evaluate cognitive functions, the Glasgow Outcome Scale-Extended (GOS-E) to assess prognosis, and the Activities of Daily Life-the Barthel Index scale (ADL-BI) to evaluate improvements in post-injury living abilities of the participants. Detailed assessment scales and operating instructions are available in **Appendix 3**.

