**Attachment 5. Glasgow Coma Scale (GCS)**

**Glasgow Coma Scale (GCS)**

| Eye Opening Response | | Language Response | | Motor Response | |
| --- | --- | --- | --- | --- | --- |
| Item | Score | Item | Score | Item | Score |
| Open eyes spontaneously | 4 | Is oriented to person, place and time | 5 | Follows commands | 6 |
| Open eyes in response to speech | 3 | Converses, may be confused | 4 | Makes localized movement in response to painful stimulation | 5 |
| Open eyes in response to painful stimulations | 2 | Replies with inappropriate words | 3 | Makes non purposeful movements in response to painful stimulation (withdraws from pain) | 4 |
| Does not open eyes in response to any stimulation | 1 | Makes incomprehensible sounds | 2 | Flexes upper extremities/ extends lower extremities in response to painful stimulation | 3 |
|  |  | Makes no response | 1 | Extends all extremities in response to painful stimulation | 2 |
|  |  |  |  | Makes no response to noxious stimulation | 1 |

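### The GCS change endpoint has a ceiling at 15 for eligible patients, and Section 14 does not list baseline GCS among the covariates although the synopsis adjusts for baseline

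*Protocol*

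**What the plan says.** - **Endpoint.** Protocol Section 7.1.2 includes "Changes in scores on the LOTCA and GCS at the end of treatment compared to baseline". The Trial Schedule has the GCS at screening and at the end of the treatment period only.
- **Who is enrolled.** Section 4.2.1 requires "Classified as mild to moderate head injury (GCS: 10-15", and Section 4.1 repeats "mild to moderate (GCS score of 10 to 15) acute TBI". The cognitive entry criterion, "MMSE score below normal, with diagnostic cutoff values depending on different educational levels", does not exclude a patient with GCS 15.
- **The scale.** The top row of Attachment 5 reads "Open eyes spontaneously | 4 | Is oriented to person, place and time | 5 | Follows commands | 6".
- **Analysis.** Section 14 states: "For the secondary continuous efficacy outcomes, mean differences with corresponding 95% CIs were also analyzed using ANCOVA". It then says that all models adjust for age, sex, education and baseline TBI severity. The baseline score of the outcome is not in that list. The same section uses TBI severity as a two-level factor (mild, moderate) for subgroups and gives no cut-off.
- **Synopsis.** Under Statistical Analyses, the ANCOVA of change from baseline adjusts for baseline, injury classification and education level. This is a different list.
- **Role of the GCS.** Section 5.8 describes it as "Use of the GCS to evaluate the severity of cranial injuries in participants". The secondary objective in Section 2 is "To analyse changes in function and disease severity of patients with TBI treated with either L-oxiracetam, oxiracetam or placebo"; it names no instrument.

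**The concern.** A change score on a bounded scale depends heavily on where the patient starts. Here the bound lies inside the eligible range: a patient at 10 can gain up to 5 points, a patient at 14 can gain 1, and a patient at 15 can gain none. Two things follow.

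First, the all-patient mean difference is a weighted average in which patients at 15 contribute no improvement. Covariate adjustment cannot create headroom that they do not have.

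Second, most of the spread in the change scores comes from the spread in baseline scores. If the model holds only a mild/moderate category, much of that spread stays in the residual and hides the treatment effect. Section 14 and the synopsis disagree on exactly this covariate.

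At stake is how a null GCS result can be read. It could mean no effect, no room to improve, or a model that left avoidable noise in the comparison.

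**Working it through.** The protocol gives no effect size, SD, power or baseline distribution for the GCS, so there is no planned figure to reproduce.

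**1. Ceiling.** Scale maximum = 4 + 5 + 6 = 15, which equals the upper limit of eligibility.

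**2. Headroom.** Let p be the share at GCS 15 (assumed), with the rest spread evenly over 10 to 14. The average gap below 15 is then (5+4+3+2+1)/5 = 3, and the mean possible gain over all patients is 3(1 − p). If only patients below 15 can gain, the all-patient difference is (1 − p) times the difference in patients below 15.

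| Share at 15 | Mean possible gain (points) | Fraction of effect retained |
|---|---|---|
| 1/6 (even spread over 10–15) | 2.5 | 83% |
| 30% | 2.1 | 70% |
| 50% | 1.5 | 50% |
| 70% | 0.9 | 30% |
| 90% | 0.3 | 10% |

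**3. Power with and without baseline GCS.** From the protocol: 236 (L-oxiracetam) against 118 (placebo), two-sided 0.05. Assumed:
- 40, 60 or 80% of patients at GCS 15
- the rest spread over 10, 11, 12, 13, 14 in proportions 1:1:2:3:3
- 90% against 75% of patients below 15 reach 15 by end of treatment
- 2% of patients at 15 fall to 14
- mild means GCS 13–15

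The result also depends on where patients who miss 15 end up, so three versions are shown. Figures are simulated power over all patients at 40/60/80% at GCS 15; repeat runs differ by up to about three points.

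| Patients who miss 15 | Baseline GCS in model | Severity category only |
|---|---|---|
| end at 14 | 77/55/28% | 16/11/6% |
| stay at baseline | 70/55/31% | 46/30/17% |
| gain one point, up to 14 | 68/52/30% | 30/19/13% |

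**4. Hand check, first row, 40% at 15.** The effect below 15 is (0.90 − 0.75) × 1 point = 0.15, so over all patients it is 0.60 × 0.15 = 0.09.

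*Severity category only.* The residual is roughly the spread of (15 − baseline) within category.
- Mild: weights 0.40, 0.18, 0.18 at gaps 0, 1, 2. Mean 0.54/0.76 = 0.711; variance 0.90/0.76 − 0.711² = 0.68.
- Moderate: weights 0.12, 0.06, 0.06 at gaps 3, 4, 5. Mean 0.90/0.24 = 3.75; variance 3.54/0.24 − 3.75² = 0.69.
- Pooled variance is about 0.68, SD 0.825. Standard error = 0.825 × √(1/236 + 1/118) = 0.825 × 0.1127 = 0.093.
- Ratio 0.09/0.093 = 0.97, giving power of about 16%.

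*Baseline GCS in the model.* What remains is roughly whether a patient ends at 14.
- Probability 0.60 × 0.10 + 0.40 × 0.02 = 0.068 against 0.60 × 0.25 + 0.008 = 0.158. Variances 0.063 and 0.133; pooled (236 × 0.063 + 118 × 0.133)/354 = 0.086, SD 0.294.
- Standard error = 0.294 × 0.1127 = 0.033. Ratio 0.09/0.033 = 2.7, giving power of about 77%.

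Both agree with the simulation.

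**5. Does restricting to patients below 15 help?** With baseline GCS in both models and patients who miss 15 ending at 14, subset power is 80/67/39% against 77/55/28%. If they stay at baseline, the gain is only about 1 to 3 points. If they gain one point, it is 69/56/34% against 68/52/30%.

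**The case against.** **Dilution is not the same as lost power.** Patients with no change also reduce the variance. Most of the fall in power from 40% to 80% at the ceiling comes from having fewer patients below 15, and no redefinition brings them back. With one in six at the ceiling, all-patient and subset power agree within simulation error. This stands, and it is why the all-patient analysis should stay.

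**The share at 15 may be small.** Every patient has intracranial bleeding and a below-normal MMSE, and 10 of the 30 MMSE points are for orientation, which the top GCS verbal score also requires. This also stands. A reader might infer that the endpoint is mostly zeros fixed by design, but that needs more than half of patients at 15 and the protocol gives no distribution. Nor are the values fixed at zero: a patient at 15 can worsen, and preventing a fall is a legitimate effect.

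**Baseline may already be intended.** The synopsis lists it, and Section 14 might mean the GCS score itself by TBI severity. If so, the power loss disappears. But Section 14 treats severity as mild versus moderate elsewhere, and its list claims to cover all models. The two sections need reconciling on their own text, whatever an unseen SAP may add.

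**The GCS is not declared the measure of disease severity.** A reader might join Sections 2 and 5.8 and conclude that the severity objective rests on this endpoint. No section says so, and several other secondary scales are listed.

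**Conclusion.** The point holds in a limited form. The ceiling follows from the protocol's own eligibility range and scale, and the all-patient mean difference shrinks to (1 − p) of the effect in patients below 15, with p unstated.

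The larger and more robust problem is the covariate list. In all three versions, leaving baseline GCS out costs much of the power: from 77/55/28% to 16/11/6% at one end, and from 70/55/31% to 46/30/17% at the other. These sizes rest on the assumed baseline distribution, recovery rates and mild/moderate cut-off; the direction does not change across the versions tried.

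The case for replacing the endpoint with a subset, or for making it descriptive only, is not made. The subset's own power gain is small in two of the three versions. The point is minor: it concerns one of several secondary endpoints and leaves the primary endpoint, LOTCA change at 90 days, untouched.

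**What to change.** - Reconcile Section 14 with the synopsis, and state that the ANCOVA of GCS change includes baseline GCS score as a covariate. Say whether TBI severity is kept beside it, and give its cut-off.
- Keep the all-patient GCS analysis.
- Add a supplementary analysis in patients with baseline GCS below 15, as mean change adjusted for baseline GCS or as the proportion reaching 15 at end of treatment. Report the number at 15 at baseline in each arm, so that a null result can be read against the ceiling.

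The covariate change is wording only. The supplementary analysis adds one comparison in a smaller subset. That subset is defined by a value measured before randomization, so the comparison within it remains randomized, but its gain in power is small and depends on assumptions.
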